## Abstract

**Background:**

Gyejibokryeong-hwan (GBH) is an herbal medicine composed of five herbs. It has been widely used to treat gynaecological diseases in traditional East Asian medicine. Recent animal studies suggest antidepressant effects of GBH. In this trial, we explore the efficacy and safety of GBH in patients with major depressive disorder and to identify the optimal dose for the next phase III trial.

**Methods:**

This trial will enrol 126 patients diagnosed with major depressive disorder and not treated with antidepressants. Participants will be randomised to receive a high or a low dose of GBH or placebo granules. The study drugs will be administered three times a day, for 8 weeks. The 17-item Hamilton Depression Rating Scale (HDRS) will be used to measure the severity of depressive symptoms at weeks 2, 4, 6, 8, and 12. The primary efficacy endpoint is the change from baseline in HDRS-17 total score post-treatment at week 8. Analysis of covariance will be based on the baseline HDRS-17 total score and site as the covariates. Safety assessment will be based on the frequency of adverse events. The severity and causality of the study drug will be assessed.

**Discussion:**

This study is designed to evaluate the efficacy and safety of GBH granules compared with placebo in patients with major depressive disorder.

**Trial registration:**

Clinical Research Information Service KCT0004417. Registered on November 1, 2019 (prospective registration)

## Administrative information

Note: The numbers in curly brackets in this protocol refer to SPIRIT checklist items. (http://www.equator-network.org/reporting-guidelines/spirit-2013-statement-defining-standard-protocol-items-for-clinical-trials/).

## Introduction

### Background and rationale {6a}

Major depressive disorder (MDD) is one of the depressive disorders characterised by major depressive episodes, which are diagnosed by the presence of persistent depressed mood or anhedonia, and additional symptoms of disturbed appetite or sleep, psychomotor agitation or retardation, fatigue, feeling of worthlessness, decreased concentration, or suicidal thoughts for at least 2 weeks [1, 2]. In Korea, the reported prevalence of depression was 2.8% in 2002, and 5.3% in 2013 which has increased with time [3]. Also, the suicide rate in Korea was 24.6 per 100,000 person in 2019, which was the highest among the Organisation for Economic Cooperation and Development (OECD) countries [4]. Antidepressant monotherapy with escitalopram or sertraline is recommended as the first-line strategy for mild-to-moderate depressive disorders without psychotic features in Korea [5, 6]. Nonetheless, new medications are needed for rapid amelioration of depression with fewer side effects.

*Gyejibokryeong-hwan* (GBH, *Guizhifuling-wan* in Chinese and *Keishibukuryo-gan* in Japanese) is a representative herbal formulation of traditional East Asian medicine (TEAM). It is composed of *Cinnamomi Ramulus*, *Poria Sclerotium*, *Moutan Radicis Cortex*, *Persicae Semen*, and *Paeoniae Radix*. According to the TEAM theory, GBH is one of the herbal formulae used to treat “qi stagnation and blood stasis” syndrome. GBH has been widely used to treat various gynaecological and cardiovascular diseases, for example, primary dysmenorrhea [7], endometriosis [8], hot flashes [9], climacteric syndrome [10–13], and angina pectoris [14].

The Korea Institute of Oriental Medicine (KIOM) established the project to investigate the novel indication for ancient herbal medicines and extend the indications (“drug repositioning project of herbal medicine”). Based on in vitro and in vivo screening tests, GBH was selected as one of the best candidates for alleviating depressive symptoms. GBH showed antidepressant-like effects in mouse models of reserpine-induced depression [15]. Also, potential neuroprotective effects of GBH were reported in lipopolysaccharide-stimulated BV2 microglia [16]. We also conducted a prospective observational study of herbal medicine in patients with depressive disorder, and GBH was helpful to patients and showed clinical adaptability [17]. Also, few clinical studies reported the role of GBH in managing depressive symptoms. In the previous two clinical studies of patients with asymptomatic cerebral infarction conducted in Japan, treatment with GBH extract improved the scores on the self-rating depression scale [18]. Also, patients who were treated with GBH scored lower on the self-rating depression scale than those who were not [19]. The potential role of GBH in improving depressive symptoms in patients with cerebrovascular diseases was reported. Meanwhile, the role of GBH compared with placebo in patients with depressive disorders has yet to be elucidated. Animal and clinical studies suggested the possible effects of GBH on patients with major depressive disorders. GBH has been widely used in East Asian countries without serious risk, and the risk associated with GBH in depressive patients is expected to be low.

### Objectives {7}

The current phase II randomised controlled trial explores the efficacy and safety of high-dose and low-dose GBH compared with placebo in 126 patients with MDD. The primary objective is to explore whether at least one of the two doses of GBH is effective compared with placebo in patients with MDD. At the post-treatment phase (week 8), the changes from baseline in the 17-item Hamilton Depression Rating Scale (HDRS) total score will be compared among three groups. Subsequent pairwise comparisons will be carried out between the two groups treated with low-dose GBH and placebo, and high-dose GBH and placebo. Also, based on the effect sizes of GBH compared with placebo, which will be examined in this phase II trial, the feasibility of the phase III therapeutic confirmative clinical trial will be established. The secondary objectives include analysis of the efficacy of low-dose and high-dose GBH in patients with MDD compared with placebo based on HDRS response, HDRS remission, and changes from baseline on the HDRS-6 subscale and Beck Depression Inventory-II (BDI-II) at the post-treatment (week 8). The safety of GBH compared with placebo will be assessed based on the incidence of intervention-related adverse events, measurement of vital signs, clinical and laboratory evaluations, and electrocardiograms (ECGs).

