#### Criteria for discontinuing or modifying allocated interventions {11b}

Participants are considered for treatment cessation and elimination from the study if they meet the following criteria.Participants who do not meet inclusion and exclusion criteriaParticipants with serious adverse events (SAEs)Participants with adverse events warranting discontinuation of study drugParticipants with symptom aggravation and in need of another treatmentParticipants who withdraw consentParticipants who are lost to follow-upParticipants whose compliance with treatment is below 70%Participants who are unsuitable for continuing administration by the investigators

Additionally, procedures for assessing suicide risk of participants and discontinuing intervention in case of high suicide risk were established. During 8 weeks of treatment, the depressive symptoms of participants including suicide risk will be assessed every 2 weeks. Assessment of suicide risk will be carried out using the third item of HDRS and semi-structured interview for assessing suicide risk. High suicide risk will be determined by the researcher based on the presence of specific suicide ideation or suicide attempt. Participants with high suicide risk will be discontinued from the study immediately and transferred for appropriate management and treatment.

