### Data collection and management

#### Plans for assessment and collection of outcomes {18a}

##### Primary outcome

HDRS is a representative clinician rating scale for depression. It consists of 17 items measuring the severity of depressive symptoms, and the HDRS-17 total scores range from 0 to 52, with the higher score indicating severe symptoms [28, 29]. The Korean version of HDRS validated in 2005 will be used in this study [30]. HDRS will be evaluated by trained investigators working as fellows or residents at the Department of Neuropsychiatry in Korean medicine. To ensure the consistency of HDRS, the investigators from three sites met to conduct training and discussion sessions before the initiation of clinical trial. The HDRS assessment will be carried out according to the Structured Interview Guide for the Hamilton Depression Rating Scale (SIGH-D) [31]. HDRS will be measured every 2 weeks during the 8 weeks of administration (week 0, 2, 4, 6, 8) and follow-up assessment (week 12).

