#### Methods in analysis to handle protocol non-adherence and any statistical methods to handle missing data {20c}

##### Definition of analysis population

Full analysis set will include all randomised participants, except as follows:Participants who are found to be ineligible for the trial after randomisationParticipants who have never been exposed to the investigational productParticipants who have never been assessed after randomisation

Per protocol set will include participants who have completed the trial process without violating the protocol. The following participants will be excluded from the per protocol set.Participants who dropped out from the trialParticipants who are found to be ineligible for the trialParticipants with less than 75% compliance with the study treatment protocolParticipants who are considered as a major violation for any other reason

Safety set will include all participants who have received the intervention at least once. Participants who have never been treated with the investigational product will be excluded from the safety set.

For the efficacy outcome analysis, the full analysis set will be mainly analysed, and per protocol set will be additionally analysed. A safety set will be used for the safety analysis. Multiple imputations will be performed to handle missing data.

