#### Adverse event reporting and harms {22}

All adverse events reported by the participants or observed by the investigators will be recorded. The severity of adverse events and causality attributed to the study drug will be evaluated.

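### The Objectives tie the adverse event comparison with placebo to intervention-related events; all treatment-emergent events should be the main count

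*Protocol article*

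**What the plan says.** The Objectives section {7} is the only place in the article that links an adverse event count to the placebo comparison: "The safety of GBH compared with placebo will be assessed based on the incidence of intervention-related adverse events". The same sentence goes on to list vital signs, clinical and laboratory evaluations and ECGs as further bases for the comparison.

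The Methods part of the Abstract words the measure more broadly: "Safety assessment will be based on the frequency of adverse events". Causality follows there as its own item: "The severity and causality of the study drug will be assessed".

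The section on adverse event reporting and harms {22} covers collection: "All adverse events reported by the participants or observed by the investigators will be recorded". It adds: "The severity of adverse events and causality attributed to the study drug will be evaluated". It does not say that causality restricts what is compared.

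The population for safety is set under Definition of analysis population: "Safety set will include all participants who have received the intervention at least once". That section names no adverse event measure.

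**The concern.** In a randomised, placebo-controlled trial, the placebo arm shows what the background rate of events would have been. A comparison of all events between arms needs no judgement about the cause of any single event. Once the compared count is restricted to events rated as related, the result also depends on how raters assign cause. A participant can be in the safety set and have a recorded event, yet add nothing to the compared count because the event was rated unrelated.

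What is at stake is the adverse event incidence and risk difference shown for each GBH dose against placebo. These are part of the safety picture that a phase II trial passes on to phase III planning. If the main count is not fixed as all events, the safety message can vary with rater judgement, and the article gives no information on how accurate that judgement is.

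**Working it through.** **Step 1: the sections side by side.**

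| Section | Adverse event count | Comparator in that sentence | Role of causality |
|---|---|---|---|
| Objectives {7} | related events | placebo | decides which events count |
| Abstract, Methods | adverse events | none named | assessed separately |
| Harms {22} | all events recorded | none named | evaluated for events |
| Definition of analysis population | none named | none named | not mentioned |

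Related events are a subset of all recorded events, so the sentences can all be met by showing both counts. Read alone, however, the Objectives wording makes the filtered count the comparison with placebo, and no other section makes the unfiltered one that comparison.

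**Step 2: does the filter matter, and in which direction?** The plan has no adverse event figure to reproduce. The only input taken from the article is 42 recruited per group (Sample size {14}). Everything else here is assumed.

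- p1 and p0 are the true incidences on active drug and placebo.
- b is the share of background events rated related. It is taken as equal in both arms, as blinding would suggest.
- e is the share of drug-caused excess events rated related.

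The formulas are:

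- related incidence on placebo: pP = p0 × b
- related incidence on active drug: pA = p0 × b + (p1 − p0) × e
- difference: pA − pP = (p1 − p0) × e
- z = difference / √{[pA(1 − pA) + pP(1 − pP)] / 42}

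Worked row with p1 = 0.15, p0 = 0.05, b = 0.2, e = 0.7:

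- pP = 0.05 × 0.2 = 0.01
- pA = 0.01 + 0.10 × 0.7 = 0.08
- z = 0.07 / √[(0.0736 + 0.0099) / 42] = 0.07 / 0.0446 = 1.57

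| Count | b | e | Active | Placebo | Difference (points) | z |
|---|---|---|---|---|---|---|
| All events | 1 | 1 | 15% | 5% | 10 | 1.55 |
| Related, rating uninformative | 0.5 | 0.5 | 7.5% | 2.5% | 5 | 1.06 |
| Related, rating uninformative | 0.3 | 0.3 | 4.5% | 1.5% | 3 | 0.81 |
| Related, rating uninformative | 0.1 | 0.1 | 1.5% | 0.5% | 1 | 0.46 |
| Related, partly informative | 0.2 | 0.5 | 6% | 1% | 5 | 1.26 |
| Related, informative | 0.2 | 0.7 | 8% | 1% | 7 | 1.57 |
| Related, highly informative | 0.1 | 0.9 | 9.5% | 0.5% | 9 | 1.93 |

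For more common events (40% versus 25%), the all-event difference is 15 points with z 1.49. It becomes 4.5 points with z 0.70 at b = e = 0.3, and 10.5 points with z 1.61 at b = 0.2, e = 0.7.

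**Step 3: reading the table.** In this model the difference in points is multiplied by e, so it can only stay the same or shrink. The difference relative to its noise can go either way: it falls when ratings carry little information about cause, and it is kept or improved when they carry much. The table therefore shows that the related-event result depends on b and e, both unknown. It does not show a definite loss. The all-event row involves neither b nor e.

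**The case against.** The case for leaving the text alone is substantial.

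- **The sentences are compatible.** A reader might infer that the article sets out two contradictory comparisons, or that events rated unrelated are thrown away. Neither follows. The Abstract sentence names no comparator, the Objectives do not say that related events are the only count, and the harms section keeps every event in the record. This stands.
- **The filter touches one component.** The same Objectives sentence also compares vital signs, clinical and laboratory evaluations and ECGs, with no causality condition. Serious adverse events are a ground for stopping treatment under {11b} whatever their cause. This stands.
- **Investigators are blinded {17a}.** If they are the ones rating causality, the filter should not favour an arm by design while blinding holds. This stands. It does not prevent a true drug effect from being rated unrelated in some participants.
- **Related events can be the sharper count.** With good raters the filter removes background noise, as the last two rows of the table show. This stands, and it is a reason to keep the related-event count beside the main one.
- **The article is condensed.** Adverse event tables are usually laid out in the full protocol or analysis plan, and both counts may appear there. This answers any complaint that detail is absent. It does not answer the present point, which is that the measure the Objectives do state is the weaker choice for the main comparison.

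**Conclusion.** The point holds as a cheap improvement worth considering, and it does not threaten the trial. The stated adverse event comparison with placebo rests on a causality-filtered count, although the all-event count is already collected and needs no judgement about cause.

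The effect is limited to the adverse event count. Its size and direction cannot be given, because the article reports no event rates and no share of events judged related. The figures above rest on assumed rates and on equal rating behaviour in both arms. In the 15% versus 5% example no z reaches 1.96 under either count, and the article states no adverse event test that would depend on the choice. What changes is the displayed incidence and risk difference.

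A reader might also infer that worsening depression or suicidality could escape notice by being rated unrelated. The documents do not support that. On suicide risk, section {11b} states: "Assessment of suicide risk will be carried out using the third item of HDRS", with a semi-structured interview, every 2 weeks during treatment. On symptoms, section {18a} states: "HDRS will be measured every 2 weeks during the 8 weeks of administration", with a further rating at week 12. Neither passes through a causality rating.

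**What to change.** Reword the adverse event part of the safety objective. The main comparison with placebo should be the incidence of all treatment-emergent adverse events, by arm, in the safety set, regardless of causality. Present intervention-related events next to it as a supportive count. Leave the vital sign, laboratory and ECG components as they are.

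The cost is one phrase in the Objectives. All events and their causality ratings are already to be collected under {22}, so no visits, data items or procedures are added. The small downside is that the main count will contain more background events; the supportive count beside it addresses that. The change should be made before unblinding, so that the choice of main count cannot be influenced by the results.

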### Trial design {8}

This study will be a randomised, double-blind, placebo-controlled, and multi-arm parallel-group trial. Participants will be allocated in a 1:1:1 ratio to one of three parallel groups: high-dose GBH, low-dose GBH, and placebo. The HDRS-17 total scores in high-dose and low-dose GBH groups will be compared with those of the placebo group.

## Methods: participants, interventions, and outcomes

### Study setting {9}

This study is being conducted at three university hospitals in Korea specialising in Korean medicine. Two sites are located in Seoul and one site in Daejeon.

### Eligibility criteria {10}

#### Inclusion criteria

Men and women aged 19 to 65 yearsThose diagnosed with major depressive disorder based on DSM-5 (Diagnostic and Statistical Manual of Mental Disorders-5) criteriaThose with a HDRS-17 total score of 18 or higherThose who volunteered to participate and sign the agreement

#### Exclusion criteria

Participants with risks of suicideParticipants with major depressive disorder who need hospitalisationParticipants who received electroconvulsive therapy (ECT), vagal nerve stimulation (VNS), deep brain stimulation (DBS), light therapy, or transcranial magnetic stimulation (TMS) within 3 months prior to studyParticipants who are diagnosed with and are being treated for panic disorder, obsessive disorder, post-traumatic stress disorder, or personality disorderParticipants with a history of manic, schizophrenic, or mixed episodesParticipants with current or lifetime alcohol or other substance abuse/dependenceParticipants who are undergoing treatment with medicines or substances that may affect the degree of depression (e.g., anxiolytics, antidepressants, antipsychotics, corticosteroids, female hormones, L-dopa, digitalis, bromide, cyclosporin, disulfiram, isoniazid, and yohimbine) within 4 weeksParticipants who are undergoing taking antiplatelet therapyParticipants with a medical condition that may affect the degree of depression, including myocardial infarction, brain tumour, multiple sclerosis, pancreatic disease, hypo/hyperthyroidism, hyperparathyroidism, Addison’s disease, Cushing’s disease, rheumatoid arthritis, cancer, cerebrovascular disease, dementia, and epilepsyParticipants with chronic illnesses such as chronic active hepatitis, hypertension, and diabetes that are not well-controlled with appropriate treatmentParticipants who are being treated for liver cancer, liver cirrhosis, chronic kidney failure, or congestive heart failure classified as NYHA class III–IVParticipants with liver dysfunction or renal impairment (based on ALT, AST, ALP ≥ twice the normal upper limit or creatinine > 2.0 mg/dL at screening)Participants with hereditary conditions such as galactose intolerance, Lapp lactase deficiency, or glucose-galactose malabsorptionParticipants carrying diseases that may affect the absorption of the drug or who manifest a digestive disorder after surgeryParticipants who involved in other clinical trials within 1 monthParticipants with hypersensitivity reactions and allergies to research drugsParticipants who are taking other herbal medicinesParticipants who are unable to understand the consent form due to cognitive defects such as mental retardation or intellectual problemsPregnant or lactating womenParticipants who are likely to be pregnant and who do not agree to the approved methods of contraception (double contraception, intrauterine contraceptive, and spermicide) during the trialParticipants who are determined as unsuitable by the investigator

### Who will take informed consent? {26a}

The principal investigators, who are professors in the Department of Neuropsychiatry at Korean medicine hospitals, or sub-investigators, who are fellows or residents in the hospital and delegated by the principal investigators, will explain the clinical trial and the study drug in detail and seek informed consent for participation in the clinical trial. Participants will be informed that the effect of study drug is not validated, and placebo can be administered without active ingredient. Also, the standard treatment for patients with depressive disorders will be described in the informed consent form and explained by the investigators. Participants will be intensively educated to contact the investigators whenever they suspect severe depressive symptoms. The consent will be obtained prior to the screening process.

### Additional consent provisions for collection and use of participant data and biological specimens {26b}

Not applicable

### Interventions

#### Explanation for the choice of comparators {6b}

Placebo granules, which are identical to the experimental granules in shape, colour, scent, and taste and containing no active ingredients, will be used as comparators. Placebo granules will be produced and packaged by Hanpoong Pharm & Food Co., Ltd., (Jeonju, Korea) under good manufacturing practice (GMP) regulations of Korea. Placebo granules will consist of lactose hydrate, corn starch, hydroxypropyl methylcellulose, and caramel colour. Three placebo granule sachets (1.5 g for each, total 4.5 g) will be orally administered twice a day, for 8 weeks to participants in the placebo group.

